## Sample calculation

The sample size was calculated to ensure a 95% test power. It was determined that with 32 individuals and an effect size of 0.8, the test power would be 0.9566, thereby maintaining the significance level at  $\alpha = 0.05$  (Figure 1).

[figure not shown]

Figure 1

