# **Effect of photobiomodulation treatment in the sublingual, radial artery region, and along the spinal column in individuals with multiple sclerosis: Protocol for a randomized, controlled, double-blind, clinical trial**

## **Abstract**

**Background:** Multiple sclerosis (MS) is an autoimmune disease, for which the forms of treatment are medication and rehabilitation. However, *in vitro* and *in vivo* studies have demonstrated that photobiomodulation can be an effective treatment modality for inflammatory diseases, including MS. Photobiomodulation has a broad range of benefits, such as the avoidance of cell and tissue death, the stimulation of healing and injury repair, reductions in pain, edema and inflammation, cell proliferation and even apoptosis. The outcomes of photobiomodulation include the regeneration of cells, the stimulation of the growth of Schwann cells, a reduction in spasticity, functional improvements, a reduction in nitric oxide levels and the upregulation of the cytokine IL10, demonstrating that this therapeutic modality can offer neuro-protection.

**Methods:** A randomized, controlled, double-blind, clinical trial is proposed. The patients will be divided into 6 groups. Groups 1 and 2 will receive sham and active photobiomodulation in the sublingual region, respectively. Groups 3 and 4 will receive sham and active photobiomodulation along the spinal cord, respectively. Group 5 will receive placebo treatment with photobiomodulation on the skin in the region of the radial artery with a specific bracelet. Group 6 will be treated with photobiomodulation on the skin in the region of the radial artery.

**Discussion:** Treatment for MS is directed at the immune response and slowing the progression of the disease. This is one of the first clinical trials involving photobiomodulation in the sublingual region and along the spinal cord, which could help establish a promising new form of non-pharmacological treatment for autoimmune diseases. This is one of the first clinical trials with sublingual photobiomodulation and along

the spinal cord that could help establish a new form of promising treatment of the disease associated with pharmacological treatment.

**Key words:** Low-level laser therapy, photobiomodulation, multiple sclerosis, oxidative stress, physical therapy.

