Prognosis is unpredictable with regard to the disability that occurs due to the manifestations of the disease, which are normally associated with progressive locomotion impairment.[12] Treatment is directed at the immune response and slowing the progression of the disease, which can be achieved with the use of drugs.[12,13] Moreover, rehabilitation can lead to improvements in walking capacity, cognition, fatigue, depression, quality of life, participation in activities, muscle strength, cardiovascular performance, and balance.[13,14]

In vitro and in vivo studies have demonstrated that photobiomodulation is effective for inflammatory diseases, including MS.[15] This therapeutic modality has a broad range of benefits, such as the avoidance of cell and tissue death, the stimulation of healing and injury repair, reductions in pain, edema and inflammation, cell proliferation, and even apoptosis.[15,16] The outcomes of photobiomodulation include the regeneration of

cells, the stimulation of the growth of Schwann cells, a reduction in spasticity, functional improvements, a reduction in nitric oxide levels, and the upregulation of the cytokine IL10, demonstrating that this therapeutic modality can offer neuroprotection.[15,17]

The aim of the proposed study is to evaluate whether photobiomodulation in the sublingual region and along the spinal cord modulates the expression of IL-10, TNF- $\alpha$ , and nitric oxide in individuals with MS. The main objective of this study is to evaluate if the photobiomodulation along the spinal cord in the sublingual region and irradiation in the radial artery can modulate the expression of IL-10, TNF- $\alpha$ , and nitric oxide.

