## Statistical analysis

The data will be tabulated and treated using the SPSS 20.0 for Windows. Descriptive statistics will be performed. The chi-square test and Fisher's exact test will be used to test associations with the categorical variables. The Student's t-test will be used and Pearson's correlation coefficients will be calculated for the analysis of correlations among the continuous variables. The level of significance will be set at 95% ( $p < 0.05$ ).

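### The stated power of 0.9566 reproduces for a four-group ANOVA, not for the six arms and Student's t-test that the protocol describes

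*Protocol*

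**What the plan says.** The Protocol's section on the sample calculation sets the target: "The sample size was calculated to ensure a 95% test power". It then gives the result: "It was determined that with 32 individuals and an effect size of 0.8, the test power would be 0.9566", with alpha 0.05. It refers to a Figure 1, which is not shown in the text at hand. The words do not say which test was used, whether 0.8 is Cohen's d or f, how many groups were assumed, or whether 32 is the trial total.

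The design is fixed elsewhere. The Abstract says "The patients will be divided into 6 groups". The section on recruitment and randomization describes them as three sham/active pairs (sublingual, spinal, radial artery) with equal allocation. For continuous outcomes the Statistical analysis section says "The Student's t-test will be used". It names no ANOVA or other multi-group test.

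The Introduction has two aim sentences. The first covers two sites only: "The aim of the proposed study is to evaluate whether photobiomodulation in the sublingual region and along the spinal cord modulates the expression". The second adds the radial artery.

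**The concern.** A power figure is meaningful only for a given test, number of groups and effect-size metric. Here the figure can be recovered exactly, but for a design with four groups and a test that the protocol does not mention. It cannot be recovered for six arms with 32 patients, or for a t-test on 32 patients with an effect of 0.8.

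This is the protocol's only justification of its sample size. A reader told that the trial has 95% power may take a null result on IL-10, TNF-alpha or nitric oxide as evidence of no effect. With 5 or 6 patients per arm, a single active-versus-sham comparison could miss even a large difference.

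**Working it through.** **Inputs.** N = 32, effect size 0.8, alpha 0.05, stated power 0.9566 and target 95% (Sample calculation). Six arms in three sham/active pairs (Abstract; Recruitment and randomization). Student's t-test (Statistical analysis). Assumptions of this check: two-sided t-tests, equal allocation, and 32 as the trial total unless noted.

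**1. Reproducing the stated figure.** For a one-way ANOVA with k groups, power = P[F′(k−1, N−k, λ) > F(0.95; k−1, N−k)], with λ = f²N. With f = 0.8 and N = 32, λ = 0.64 × 32 = 20.48.

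| Groups k | df | Power |
|---|---|---|
| 2 | 1, 30 | 0.992 |
| 3 | 2, 29 | 0.977 |
| 4 | 3, 28 | **0.9566** |
| 5 | 4, 27 | 0.932 |
| 6 | 5, 26 | 0.903 |

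Only k = 4 matches. With six groups, the smallest N that reaches 95% at f = 0.8 is 37 (0.9505; N = 36 gives 0.943).

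**2. Trying the t-test with d = 0.8.** Two samples: noncentrality δ = d·√(n₁n₂/(n₁+n₂)), df = n₁+n₂−2. Paired: δ = d·√n, df = n−1.

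| Reading of 32 | Two-sided | One-sided |
|---|---|---|
| 16 vs 16 | 0.591 | 0.714 |
| 32 vs 32 | 0.883 | 0.936 |
| 32 paired | 0.992 | 0.997 |

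None gives 0.9566.

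**3. Converting the metric.** For two equal groups (or two equal clusters) of means, f = d/2, so f = 0.8 corresponds to d = 1.6.

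**4. Active versus own sham.** 32/6 = 5.33, so in practice four arms of 5 and two of 6 (4×5 + 2×6 = 32). Example, 5 vs 5 at d = 0.8: δ = 0.8 × √(25/10) = 1.265, df = 8, critical t = 2.306, power 0.201.

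| Per arm | d = 0.8 | d = 1.6 |
|---|---|---|
| 5 | 0.201 | 0.603 |
| 5.33 | 0.214 | 0.640 |
| 6 | 0.241 | 0.705 |
| 8 (48 in total) | 0.320 | 0.845 |

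At 5.33 per arm the detectable difference is 1.94 SD for 80% power and 2.50 SD for 95%.

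**5. Other readings.**
- Pooled active versus pooled sham, 16 vs 16: 0.591 at d = 0.8 and 0.992 at d = 1.6.
- Six-group ANOVA with 48 patients and f = 0.8: λ = 0.64 × 48 = 30.72, power 0.990.
- For scale, 95% power at d = 0.8 in one active-versus-sham t-test takes 42 per arm (0.952), or 6 × 42 = 252 patients, before any allowance for multiplicity or dropout.

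**The case against.** The strongest reply is that the text leaves open most of what determines the power.

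- **Metric.** A reader might infer that power falls from 95% to 21%. That sets f = 0.8 against d = 0.8. If the recovered calculation is right, 0.8 is f, and the like-for-like fall is from 0.957 to 0.903 on the ANOVA, or to 0.60–0.71 on the single-site t-test. The 21% stands only if the authors meant d, which the Protocol does not say.
- **Total.** That 32 is the total over six arms is the plain reading of 32 individuals, but no section states the total enrolment or the number per arm. If 8 per arm was meant (48 in total), the powers are higher. It follows only from the plain reading that 32 does not divide equally by six.
- **Comparison.** The t-test sentence does not say which arms are compared, whether the test is paired or whether shams are pooled. A separate analysis plan may settle this. Pooling 16 against 16 at d = 1.6 would exceed 95%.
- **Origin.** A reader might infer that the calculation was made for a four-arm trial and not redone when the radial-artery arms were added. The four-decimal match and the two-site aim sentence fit that history, but no passage states it, and Figure 1 might name the test and groups.

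All four limits stand, and they make the size of the shortfall conditional. They do not rescue the stated figure. None of these readings yields 0.9566 for six arms or for the t-test, and those that exceed 95% rest on pooling, a larger total or a d of 1.6, none of which the Protocol states. Nor is this detail that can wait for an analysis plan, since the Protocol itself makes the power claim.

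**Conclusion.** Wrong as written. The 0.9566 does not describe the six-arm, t-test design in the same document. It matches a four-group ANOVA with f = 0.8, which is a well-supported inference and not a documented fact.

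The size of the error depends on the reading:

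- Same ANOVA, six groups, 32 patients: 0.903 against a 95% target.
- Active versus own sham, 32 in total: 0.20 to 0.24 if 0.8 is d, 0.60 to 0.71 if it is f.
- The same comparison with 8 per arm: 0.32 or 0.84.

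The single-site comparison therefore stays below 95% with 5, 6 or 8 per arm under either metric. These figures assume a two-sided alpha of 0.05, equal arms, no dropout and no multiplicity adjustment. The Protocol does not support a flat statement that the trial has 21% power, or one fifth of what it claims.

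**What to change.** Replace the 95% and 0.9566 statements with power recalculated for six arms and the planned active-versus-sham t-test. State the total N, the number per arm, the test and its sidedness, the effect-size metric (d or f) and the detectable difference. Only the sponsor can say which total and which metric were intended.

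If 32 is the total and 0.8 is d, the text could say: 32 participants over six arms, 5 to 6 per arm; for each active-versus-sham comparison at two-sided alpha 0.05, power is 20% to 24% for a difference of 0.8 SD, and about 1.9 SD is detectable with 80% power. Under another intention, use the matching row of the tables above.

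The cost is a change of wording and, on the single-site comparison, a less favourable stated power. No extra patients are required to correct the statement. Keeping the 95% target for that comparison would be a separate decision to enlarge the trial. Calling the trial exploratory, with estimates and confidence intervals as the main result, is optional.

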### Discussion

Treatment for MS is directed at the immune response and slowing the progression of the disease. This is one of the first clinical trials involving photobiomodulation in the sublingual region and along the spinal cord, which could help establish a promising new form of non-pharmacological treatment for autoimmune diseases.

